### Follow Up Evaluations

Subjects will be followed at 6-weeks (± 14 days), 3-months (± 14 days), 6-months (± 30 days), 12-months (± 60 days) and 24-months (± 60 days). After completion of the 24-month follow-up, subjects will continue to be evaluated annually for 3 additional years (± 60 days) to gather additional long-term information. Information will be collected on the Follow-up Visit Form and the Individual forms for VAS, ODI and SF-36. The following information will be recorded as shown below.

Data collected at 6 weeks and 3 months will include:

• AP/Lateral, flexion/extension, and side bending standing x-rays

• Work status

• VAS Pain assessment (back, right and left leg)

• Oswestry Disability Index score

• Quality of life assessment (SF-36)

• Neurological assessment

• Adverse events

Data collected at 6 months will include:

• AP/Lateral, flexion/extension, and side bending standing x-rays

• Work status

• VAS Pain assessment (back, right and left leg)

• Oswestry Disability Index score

• Quality of life assessment (SF-36)

• Neurological assessment

• Range of Motion

• Adverse events

Data collected at 12 and 24 months will include:

• AP and Lateral, flexion/extension and lateral bending X-rays

• Work status

• VAS Pain assessment (back, right and left leg)

• Oswestry Disability Index score

• Quality of life assessment (SF-36)

• Neurological assessment

• Pain medication status

• Range of Motion

• Subject satisfaction

• Adverse events

The same follow-up information will be collected at subsequent annual visits through year 5 with the exception of the MRI scan and pain medication usage.

To collect data concerning the integrity of the blind, subjects will be asked at each follow-up visit if, since the prior visit, they have learned which device they received.

### Justification for Pooling Data across Centers

The proposed investigation is a multi-center trial in the US, where all centers will be trained to use the same study protocol. The appropriateness of pooling data from multiple centers is necessarily enhanced by training all participating centers to follow the same protocol, with clearly defined inclusion and exclusion criteria for study participation. However, if an interaction is present between treatment and center effects, the results will not be strictly poolable. Thus, in order to protect against improperly pooling data from all study centers, a formal analysis will be conducted to assess the appropriateness of pooling the data [8].

For the primary endpoint, a logistic regression will be constructed that models the success rate on three factors: treatment group, center, and the treatment group by center interaction. If the interaction term is significant at a two-sided α = 0.05 level of significance, then the offending center(s) will be identified and all analyses will be presented in a stratified fashion, since pooling the results would make interpretation of the trial difficult.

If, on the other hand, the interaction term is insignificant but the center term is significant, then fixed effects for center will be added to the final models for, at a minimum, the primary endpoint. Controlling for confounding center effects in this fashion is a well-accepted technique.

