## Methods/Design

The following study was reviewed and approved by the Yale University Human Investigation Committee.

The study proposed is a prospective, randomized, single-masked, controlled, multi-center clinical trial consisting of an estimated 414 subjects with single-level DDD of the lumbar spine (L4/L5, or L5/S1) who have failed to improve with conservative treatment for at least six months prior to enrollment. After enrollment, subjects will be randomized in a 2:1 ratio to either the Activ-L Disc (investigational device) or the control (Charité or ProDisc-L). Each investigational site will have a separate, blocked randomization schedule. Fifteen (15) to 20 investigational sites will participate in the investigation. Sites will be encouraged to randomize a minimum of 10 subjects per site and to implant a minimum of four control devices and sites are bound by a maximum of 64 subjects. The first three subjects at each investigational site will receive the Activ-L Disc and will be not be randomized, these patients will be outside of the trial. The purpose of these procedures will be for Surgeon training. Investigators who have already undergone training in implantation of the control disc will be selected for participation; however, for any participating investigator who has not performed at least three prior control implantations, up to three nonrandomized control implantations may also be performed prior to enrolling randomized subjects into the study. This will ensure that experience and proficiency with the implantation method for both discs is comparable. Thus, the maximum total enrollment in the study, including both randomized and nonrandomized cases, is 414 consisting of 261 Activ-L (216 randomized and 45 nonrandomized) and 153 controls (108 randomized and 45 nonrandomized controls). Please refer to figure 1.

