**Figure 1 F1:**
[figure not shown]
**Patient progression through both arms of trial**.

The hypothesis of the study is that the Activ-L Disc is non-inferior to the control (ProDisc-L or Charité) with respect to the rate of individual subject success at 24 months. Individual subject success is a composite of effectiveness and safety.

The null hypothesis for the investigation is that the success rate in the Activ-L group is more than 15% lower than the success rate in the control group. The alternative hypothesis is that the success rate in the Activ-L group is no more than 15% lower than the success rate in the control group. The hypotheses will be evaluated according to the method of Blackwelder [7].

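### Centre is adjusted for only if it tests significant, and the adjusted branch has no stated non-inferiority rule on the scale of the 15-point margin

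*Protocol article*

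**What the plan says.** Three parts of the protocol article bear on this.

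- **Methods/Design, randomisation.** "Each investigational site will have a separate, blocked randomization schedule". Site is therefore a stratification factor. "Fifteen (15) to 20 investigational sites will participate in the investigation", with 2:1 allocation.
- **Methods/Design, hypotheses (after Figure 1).** The null to be rejected reads: "the success rate in the Activ-L group is more than 15% lower than the success rate in the control group". Blackwelder's test is the one named for it, which is a comparison of two proportions on the difference scale, with no covariates.
- **Justification for Pooling Data across Centers.** A logistic regression for the primary endpoint contains treatment, centre and their interaction. There are three outcomes. If the interaction is significant at two-sided 0.05, results are presented by stratum. If "the interaction term is insignificant but the center term is significant, then fixed effects for center will be added to the final models", this applies at least to the primary endpoint. If neither term is significant, centre is not used.

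**The concern.** The site factor is built into the randomisation but enters the primary analysis only after a significance test on the same outcome data. The primary analysis is thus selected rather than fixed.

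The branches also differ in what they deliver. Without centre, there is a Blackwelder test with a clear rule: a difference compared with 15 points. With centre, the only model the article names is logistic, and Blackwelder's test has no model to which fixed effects could be added. A logistic model with centre effects naturally yields a conditional odds ratio. The article gives no odds-ratio margin and no step from the model back to a difference in success rates. If the centre term is significant, a reader cannot tell from the article what result would establish non-inferiority, and that choice could be made after the data are seen.

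**Working it through.** **Inputs from the article.** Margin of 15 points (hypotheses); 15 to 20 sites and 2:1 allocation (Methods/Design); 178 and 89 subjects (Power Analysis, Table 2); control success of 50-80%. The article gives that last range for its superiority power calculation; it is borrowed here for the composite endpoint.

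**The plan's own figure.** Table 2 states power of 0.8000 in all seven rows. A pooled-variance Z test with 178/89 at two-sided 0.05 gives 0.7997 to 0.8002, so the table reproduces. Nothing in this point disputes it.

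**Step 1: the margin on the odds-ratio scale.** With control rate p and Activ-L rate p - 0.15, OR = [(p - 0.15)/(1.15 - p)] / [p/(1 - p)].

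| Control rate | Activ-L rate | OR equal to a 15-point deficit |
|---|---|---|
| 50% | 35% | 0.538 |
| 55% | 40% | 0.545 |
| 60% | 45% | 0.545 |
| 65% | 50% | 0.538 |
| 70% | 55% | 0.524 |
| 75% | 60% | 0.500 |
| 80% | 65% | 0.464 |

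No single odds ratio represents the hypothesis. For example, a margin of 0.538 allows 15.0 points at a control rate of 50%. At 80% the control odds are 4, so the Activ-L odds are 0.538 × 4 = 2.15, the rate is 2.15/3.15 = 68.3%, and the allowed deficit is 80 - 68.3 = 11.7 points.

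**Step 2: how often each branch is used.** Assumptions not in the article: typical-site success of 70%, site logits varying normally with a chosen SD, one-sided 0.025 for the primary test, and a 5% likelihood-ratio test of centre (the article states a level only for the interaction). There were 20,000 simulated trials per cell. A logit SD of 0.5 puts sites one SD from typical at logits 0.847 ± 0.5, that is, success of about 59% and 79%.

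- Logit SD 0.5: centre is significant in about 58-59% of trials.
- A separate simulation with 18 sites, a 60% control rate, a between-site SD of 0.10 on the probability scale and a Pearson test gave 40-44%.

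**Step 3: operating characteristics of the stated rule.** The unadjusted test rejects when (P1 - P2 + 0.15)/SE exceeds 1.96. The stratified estimate is d = Σ w_k(p1k - p2k)/Σ w_k with w_k = n1k·n2k/(n1k + n2k) (Mantel-Haenszel, Sato variance). It stands in for the centre-adjusted branch, because the article gives no rule that could be simulated directly.

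| Logit SD | Power, stated rule | Power, always stratified |
|---|---|---|
| 0.5 | 73.6-73.8% | 73.8-74.0% |
| 0.8 | about 75.6% | about 75.6% |

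A smaller run of 6,000 trials per cell gave a gap of up to 0.3 points (72.1% against 72.4%). Type I error of the rule was 0.022-0.026 against 0.025. In the 18-site simulation it was 0.023-0.027; the 0.027 arose with no site variation, where the unadjusted test alone also gave 0.027.

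**Step 4: a test that never adjusts, for comparison.** At SD 0.5 it has 71.5-72.1% power against 73.2-73.8% stratified. At SD 0.8 it has 71.6-72.5% against 75.3-76.0%. With no site variation the two agree to within 0.1 point. These figures come from 6,000 trials per cell.

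**The case against.** The strongest reply has four parts.

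*The rule adjusts when adjustment matters.* This stands. A reader might infer from by-site randomisation that the plan gives up 2-4 points of power. That loss belongs to a test that never adjusts. The stated rule brings centre in mostly when sites differ, and its loss is about 0-0.3 points.

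*No error-rate harm is shown.* This also stands. A reader might expect a pre-test to inflate type I error, but the simulations do not show it. Where centre is ignored although sites differ, the unadjusted test is conservative (0.017 at a probability-scale SD of 0.20), which does not favour a false claim. With no true centre effect, a chance-significant centre term has almost no consequence, because both analyses then perform alike.

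*The article does not say that the final models are logistic.* This is literally true. That the adjusted analysis is logistic is an inference, though the natural one, since no other model is named. A logistic model can also yield a risk difference by standardisation, and an analysis plan that is not shown may say so. The statement that the trial will test an odds ratio would therefore go too far.

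*The branching is written in advance, so it is pre-specified.* This is partly right: the branch conditions are stated. The decision rule inside the adjusted branch is not. The selection rule is already fixed in the article, so it is not a detail left for later.

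**Conclusion.** The point holds in limited form. The article randomises by site and fixes its margin as a difference of 15 points. It then makes centre adjustment depend on a test of the same data and names for that purpose only a model on whose natural scale the margin has no fixed value (0.464 to 0.545). Under moderate site variation the adjusted branch would be used in roughly half of trials (40-59% across the two simulations), and it has no stated non-inferiority criterion.

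The documents do not support a claim of type I error inflation or of material power loss. Both statements depend on reading the adjusted branch as a stratified risk difference; for an odds-ratio analysis the question cannot be answered, because no margin is given. The frequencies rest on the assumed site variation, success rate, one-sided 0.025 level and Table 2 sample sizes. Severity is minor to moderate: the gain from a change is one unambiguous rule, not a large improvement in performance.

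**What to change.** State one primary analysis that applies whatever the centre p-value: a site-stratified risk difference for 24-month success, either Mantel-Haenszel or standardised from a centre-adjusted logistic model, with the choice between them made now. Claim non-inferiority if its lower confidence bound exceeds -15 percentage points, and state the confidence level. Combine small sites by a rule set before unmasking. Remove the step that adds centre only when it is significant.

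Keep the treatment-by-centre interaction test as a supportive check of poolability, with site-level results shown alongside the primary estimate. Report the unadjusted Blackwelder test as a sensitivity analysis.

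The cost is wording and the small-site rule. There is no change to sample size or conduct, and essentially no loss of power when sites do not differ (agreement within 0.1 point).

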## Discussion

Present treatment for disc degeneration ranges from conservative modalities, such as rest, heat, electrotherapy, physical therapy, and analgesics to surgery. Currently, there are two main surgical techniques for treatment of disc degeneration: (1) nucleotomy or discectomy, i.e., excision of part or all of the degenerated disc, which is typically performed for treatment of radicular syndrome in the case of disc herniation; and (2) spinal fusion, i.e. grafting bone between the vertebrae adjacent to the degenerated disc to eliminate articulation at the damaged reduction of the intervertebral space. Rigid internal fixation may also be used to promote fusion.

The Activ-L Disc is designed to provide a new therapeutic option for treatment of degenerative disc disease as an alternative to spinal fusion to preserve function in the lumbar vertebral region. By allowing motion at the diseased segment the replacement disc would limit the advance of adjacent level disease as well as preclude the need for fusion.

The Activ-L, ProDisc-L and Charité devices are designed to provide a treatment modality as an alternative to fusion [9]. These devices are modular systems and are intended to be used as intervertebral dynamic disc spacers in the lumbar vertebral region at the L3/L4 (ProDisc-L only), L4/L5 and L5/S1 levels.

Our study will further allow the generation of results comparing fusions with the two types of disc replacements in treating degeneration in the lumbar spine. The results will have a relevant impact on providing additional safety and efficacy data in regards to a promising alternative to lumbar spine fusions.
